### Randomization

2.6

Participants is randomly allocated to the controlled and TCM group with random number table. Numbers are generated and kept by a certain researcher who has no direct contact with the study participant. The randomized numbers will be kept in sealed envelopes, and random allocation will be conducted by opening an envelope as the researcher is informed of a participant's registration number. Before the randomization allocation, participants will be informed that they will be assigned to one of the 2 groups.

### Blind

2.7

Because TCM syndrome differentiation is needed during the research process, in this trial only participants and the laboratory technicians as well as the biostatisticians responsible for the statistical analysis will be blinded to the assigned treatments.

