#### Placebo group

2.4.3

The placebo is made up by 10% of the Chinese herbs mixture, food color, and artificial flavors. Except for the dispensing technician, researchers and patients do not know the content of the drug packages.

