### Outcome measures

2.8

The primary outcome measure for this study is renal function and including estimated glomerular filtrate rate (eGFR), serum creatinine (Scr), blood urea nitrogen (BUN) and urinary protein creatinine ratio. They will be measured every 2 to 4 week.

The secondary outcomes include TCM symptoms changes (Table 2), cardiovascular function, lipid profile including triglyceride (TG), total cholesterol (TC), low density lipoprotein (LDL), high density lipoprotein (HDL), as well as serum levels of inflammatory mediators [i.e., TNF-α, IL-1β, IL-8, monocyte chemotactic protein-1 (MCP-1)].

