**Table 2 T2:**

Evaluation of treatment efficacy by TCM syndrome scoring and Ccr and Scr variation.

Safety assessment: blood routine, liver function [i.e., alanine transaminase (ALT) and aspartate transaminase (AST)] and blood coagulation (Fig. 2).

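### Sections 2.4.3 and 2.7 give incompatible blinding rules, and if 2.7 governs, the researchers who assess TCM symptoms may know the arm

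*Protocol article*

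**What the plan says.** Two sections of the protocol article state who is blinded.

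- Section 2.4.3 (Placebo group): "Except for the dispensing technician, researchers and patients do not know the content of the drug packages". The placebo is made to resemble the decoction: "The placebo is made up by 10% of the Chinese herbs mixture, food color, and artificial flavors".
- Section 2.7 (Blind): "only participants and the laboratory technicians as well as the biostatisticians responsible for the statistical analysis will be blinded". The reason precedes it in the same sentence: "Because TCM syndrome differentiation is needed during the research process".

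The outcomes that involve TCM assessment are in section 2.8 (Outcome measures): "The secondary outcomes include TCM symptoms changes (Table 2), cardiovascular function". The caption of Table 2 reads "Evaluation of treatment efficacy by TCM syndrome scoring and Ccr and Scr variation". The abstract also names TCM symptoms beside renal function as a basis for judging efficacy.

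Section 2.6 (Randomization) has a researcher without participant contact generate and hold the random numbers. These are kept in sealed envelopes, and an envelope is opened when a participant is registered.

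**The concern.** Section 2.4.3 counts the researchers among the blinded. Section 2.7 leaves them out by a closed list that begins with the word only. A reader cannot tell whether the staff who assess or treat participants are meant to be blinded, and the trial could be run or reported under either rule.

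The conflict matters most for the TCM symptom outcome, because the exception in 2.7 is tied to TCM assessment, the same kind of activity that yields that outcome. Symptom scoring involves judgement, and an assessor who knows the arm can shift it without intending to. There are two indirect routes to the renal outcomes. Basic treatment (2.4.1) includes management that can be adjusted during the trial, and researchers may remove participants at their discretion on grounds of safety or trial quality (2.11).

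**Working it through.** The plan gives no figure on this point, so the check is a comparison of sections.

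**Step 1: is there a contradiction?**

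| Role | Section 2.4.3 | Section 2.7 |
|---|---|---|
| Participants | blinded | blinded |
| Researchers (assessing, treating) | blinded | not on the closed list |
| Laboratory technicians | not named separately | blinded |
| Biostatisticians | not named separately | blinded |
| Dispensing technician | not blinded | not on the list |

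The second row cannot be reconciled. Section 2.4.3 speaks of researchers without qualification and allows one exception; 2.7 leaves them outside the blind. Both are current text.

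**Step 2: does the stated reason require unblinding?** Differentiation could require knowledge of the arm in two ways.

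- *If it determined the prescription.* It does not. Section 2.4.2 gives one list of herbs with fixed weights for all TCM-group patients and no syndrome-based modification.
- *If it could not be done without knowing the treatment.* It can. Section 2.3.2 defines the syndrome by primary and secondary symptoms seen in or reported by the patient.

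The reason therefore does not support the exception.

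**Step 3: which outcomes are exposed if 2.7 governs?**

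- *TCM symptom change (secondary) and the TCM part of Table 2:* directly, to the extent that researchers do the scoring.
- *eGFR, Scr, BUN and urinary protein creatinine ratio (primary):* these are laboratory measures, and 2.7 blinds the laboratory technicians. Only the indirect routes through 2.4.1 and 2.11 remain.

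**Step 4: how large could the effect be?** The document gives no basis for an estimate. The following only illustrates sensitivity. It assumes a continuous symptom score compared between two groups, a two-sided 5% test and no true effect.

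- Evaluable per arm: 49 × (1 − 0.20) = 39.2, taken as 39 (group size and drop-out from section 2.5).
- Standard error of a standardised difference: √(2/39) = 0.226.
- Rejection probability for a scoring shift of b SD: Φ(−1.96 + b/0.226) + Φ(−1.96 − b/0.226).

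| Assumed shift b | b/0.226 | False-positive rate |
|---|---|---|
| 0.10 SD | 0.44 | about 7% |
| 0.25 SD | 1.10 | about 20% |
| 0.50 SD | 2.21 | about 60% |

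The shifts are assumptions, not values from the document. The content of Table 2 is not shown, so the scale that will be analysed is unknown.

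**The case against.** The strongest reply is that nothing shows anyone will in fact be unblinded. Under 2.4.3 the researchers do not know the arm. To say that they do is to take one side of a contradiction as settled. The article does not name who scores symptoms or who gives basic treatment. Section 2.10 has participants, who are blinded under both sections, fill in an evaluation questionnaire, so part or all of the symptom score may be self-reported. The primary outcomes are laboratory values run by blinded technicians.

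All of this stands, and it limits the consequence. It does not remove the contradiction or repair the reason in 2.7. As the dedicated section on blinding, with an explicit reason, 2.7 may well be the rule that is followed.

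Three stronger readings are tempting but unsupported:

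- *That the assessing and treating staff know the arm.* This holds only if 2.7 governs, and these staff are not identified.
- *That the main renal result is biased.* The route through co-treatment or removal of participants is possible, but nothing in the document shows that it operates.
- *That the envelopes disclose the arm.* Section 2.6 describes them as holding randomized numbers and does not mention arm names. It also does not say that the number conceals the arm.

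**Conclusion.** The contradiction between 2.4.3 and 2.7 is certain and must be resolved. The reason given in 2.7 does not hold on the trial's own design, with its symptom-based differentiation and fixed formula.

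The consequence is conditional. If 2.7 governs and researchers score TCM symptoms, the secondary TCM outcome and its use in Table 2 are open to direct assessor bias that a blind could have prevented, although a placebo and a dispensing technician are already provided. For the primary renal outcomes the risk is indirect only. The amount of bias cannot be derived from the document, and the percentages above show sensitivity to assumed shifts, not an expected error.

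**What to change.** - **Section 2.7:** rewrite it to match 2.4.3. Researchers who assess TCM symptoms or treat participants are blinded, together with participants, laboratory technicians and biostatisticians. Delete the syndrome-differentiation exception.
- **Who knows the allocation:** limit this to the dispensing technician and the no-contact researcher of section 2.6 who generates and keeps the numbers. Naming the technician alone would create a new conflict with 2.6.
- **Section 2.6:** state that the opened envelope shows only a number that does not reveal the arm.

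**Cost:** if 2.4.3 already describes practice, this is a change of wording. If unblinded practice was intended, it needs a small operational change to package labelling and dispensing, since the article does not say that the packages are coded. No extra staff are needed, because the placebo and the dispensing technician already exist. The change has to be made before outcomes are assessed, because scores given with knowledge of the arm cannot be repaired afterwards.

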### Outcome measures

2.8

The primary outcome measure for this study is renal function and including estimated glomerular filtrate rate (eGFR), serum creatinine (Scr), blood urea nitrogen (BUN) and urinary protein creatinine ratio. They will be measured every 2 to 4 week.

The secondary outcomes include TCM symptoms changes (Table 2), cardiovascular function, lipid profile including triglyceride (TG), total cholesterol (TC), low density lipoprotein (LDL), high density lipoprotein (HDL), as well as serum levels of inflammatory mediators [i.e., TNF-α, IL-1β, IL-8, monocyte chemotactic protein-1 (MCP-1)].

**Table 2 T2:**

Evaluation of treatment efficacy by TCM syndrome scoring and Ccr and Scr variation.

Safety assessment: blood routine, liver function [i.e., alanine transaminase (ALT) and aspartate transaminase (AST)] and blood coagulation (Fig. 2).

**Figure 2 F2:**
[figure not shown]
Schedule of enrollment, interventions and assessments.

### Statistical analysis

2.9

Data analysis will be conducted with SPSS 15.0 for windows by professionals. The quantitative data are presented as mean ± standard deviation and analyzed by analysis of variance when normally distributed. Non-parametric data will be analyzed by Wilcoxon test. A paired *t* test will be used to analyze within the groups. A *P* value of less than .05 is considered as significant.

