### Sample size

2.5

Sample size is determined for *t* test. To obtain a power of 90% (α = 0.05), and considering a drop-out rate of 20%, the total sample size required is determined to be 98, 49 in each group.

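### The between-arm comparison is not adjusted for baseline renal function and the outcome form (value or change) is left open; within-arm paired t tests cannot fill the gap

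*Protocol article*

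**What the plan says.** Section 2.9 (Statistical analysis) of the protocol article fixes four things.

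- Between arms, for normally distributed data: "The quantitative data are presented as mean ± standard deviation and analyzed by analysis of variance when normally distributed".
- Otherwise: "Non-parametric data will be analyzed by Wilcoxon test".
- Within arms: "A paired *t* test will be used to analyze within the groups".
- Threshold: "A *P* value of less than .05 is considered as significant".

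It names no baseline covariate. It does not say whether the analysed variable is the follow-up value or the change from baseline.

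Three other sections bear on the point. Section 2.3.3 admits patients with GFR from 30 to 89. Section 2.8 lists eGFR, serum creatinine, BUN and the urinary protein creatinine ratio (UPCR) as primary, and says of them: "They will be measured every 2 to 4 week". Section 2.5 sizes the trial for a t test at 90% power and alpha 0.05 with 20% dropout, giving 49 per arm.

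**The concern.** Patients enter with very different renal function, and a patient's later eGFR depends strongly on where that patient started. A comparison of follow-up values that leaves baseline out carries this spread in its error term. Comparing changes removes much of it, and ANCOVA on baseline removes at least as much as either. Section 2.9 does not choose between the first two and does not offer the third. With about 39 evaluable patients per arm, the choice can decide whether a moderate effect is detected.

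Two further features weaken the section.

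- **Within-arm tests.** The objective in section 2.2 is a contrast between treatment with and without the decoction. A paired t test inside one arm does not estimate that contrast. Both arms receive basic treatment (section 2.4.1) and are selected for symptoms (section 2.3.3), so both may change without any effect of the decoction. A significant P value in one arm and not in the other could be misread as efficacy.
- **Test chosen from the data.** Whether ANOVA or Wilcoxon is used depends on the observed distribution, so the primary test and the quantity it addresses are not settled in advance.

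**Working it through.** **1. The plan's own figure.** Section 2.5 gives 49 per arm but no difference and no SD, so the figure can only be back-solved. Evaluable per arm: 49 × 0.8 = 39.2. At 90% power and two-sided 0.05 (sidedness is not stated), the implied standardised difference is (1.960 + 1.282) × √(2/39.2) = 0.73 by the normal approximation, or 0.74 by the exact t. For example, d = 0.75 needs 39 per arm, and 39/0.8 = 48.75, rounded up to 49. The size is attainable for a t test; the effect behind it is not stated. I use 39 evaluable per arm below.

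**2. Inputs that the documents do not give.** The correlation r between baseline and follow-up is assumed to be 0.5 to 0.9, with equal SDs at both times. To see what that range means for eGFR, suppose baseline GFR is uniform on 30 to 89 (also an assumption). Its SD is 59/√12 = 17.0. The SD of the change is 17.0 × √(2(1 − r)), which is 17.0 at r = 0.5 and 7.6 at r = 0.9. An SD of change of 10 corresponds to r = 1 − 100/(2 × 17.0²) = 0.83.

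**3. Variance of the between-arm estimate**, relative to comparing follow-up values:

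- change score: 2(1 − r)
- ANCOVA: 1 − r²
- ANCOVA relative to change score: (1 − r²)/(2(1 − r)) = (1 + r)/2

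| r | Change ÷ follow-up | ANCOVA ÷ follow-up | ANCOVA ÷ change |
|---|---|---|---|
| 0.5 | 1.00 | 0.75 | 0.75 |
| 0.6 | 0.80 | 0.64 | 0.80 |
| 0.7 | 0.60 | 0.51 | 0.85 |
| 0.8 | 0.40 | 0.36 | 0.90 |
| 0.9 | 0.20 | 0.19 | 0.95 |

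ANCOVA therefore saves 25% to 81% of the variance against follow-up values, rising with r. Against change scores it saves 25% to 5%, falling with r.

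**4. Power** at a true difference of 0.4 SD of the follow-up value (illustrative), 39 per arm, two-sided 0.05, noncentral t. The standardised difference is 0.4 for follow-up values, 0.4/√(2(1 − r)) for changes and 0.4/√(1 − r²) for ANCOVA. The one degree of freedom spent on the covariate is ignored.

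| r | Follow-up values | Change | ANCOVA |
|---|---|---|---|
| 0.5 | 0.415 | 0.415 | 0.522 |
| 0.7 | 0.415 | 0.615 | 0.685 |
| 0.8 | 0.415 | 0.787 | 0.828 |
| 0.9 | 0.415 | 0.974 | 0.979 |

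**5. Within-arm tests.** Suppose both arms truly change by the same amount and each paired test has power p. The chance that exactly one arm is significant is 2p(1 − p). At p = 0.5 this is 2 × 0.5 × 0.5 = 0.50, the maximum. At p = 0.2 or 0.8 it is 2 × 0.2 × 0.8 = 0.32. At p = 0.9 it is 2 × 0.9 × 0.1 = 0.18.

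**The case against.** **The unadjusted comparison is valid.** This stands. Allocation is random (section 2.6), so the between-arm test is unbiased. Chance imbalance at baseline is already reflected in its standard error. The case for adjustment is efficiency and clear specification.

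**Covariates and models may sit in a fuller plan.** This stands in part. The article condenses a protocol, and silence on modelling detail is not a fault in itself. But section 2.9 is not silent: it names the between-arm tests, makes their choice depend on the data, and plans within-arm significance tests. Those choices can be judged as written.

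**Stronger readings that a reader might infer.**

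- *The analysis throws away most of the trial's precision.* This would need a comparison of raw follow-up values and r above about 0.71, where 1 − r² falls below one half. The article fixes neither. If changes are compared, the loss is at most 25% for r of 0.5 or more, and only 10% at r = 0.8.
- *Baseline is ignored altogether.* The paired tests presumably use baseline within arms, and the caption of Table 2 refers to variation in creatinine clearance and serum creatinine, so change enters at least one efficacy rating. What is missing is adjustment of the comparison between arms.
- *Each visit is tested separately.* The text does not say this. Analysis of variance does not exclude a repeated-measures form.
- *Efficacy will be claimed from within-arm P values.* The article states no such intention. The 50% figure is the worst case of 2p(1 − p), and it matters only if such a claim is made.

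Using Wilcoxon for non-normal data is a rule stated beforehand, and no inflation of type I error was calculated for it here. The objection to it is that a fixed scale would keep one estimand and one adjusted model.

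**Conclusion.** The point holds as one of efficiency, specification and interpretation. Section 2.9 compares the arms without baseline adjustment, leaves open whether values or changes are analysed, lets the observed distribution choose the test, and adds within-arm tests that cannot show a difference between arms.

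The size depends on which reading of section 2.9 applies. At r = 0.8 and a difference of 0.4 SD, moving to ANCOVA raises power from about 41% to 83% if follow-up values were meant, but only from 79% to 83% if changes were meant. Leaving that choice open is therefore the costlier part of the defect when r is high; at r = 0.5 changes do no better than follow-up values, and ANCOVA improves on both equally. These figures rest on the assumed correlation, equal SDs at both times, 39 evaluable per arm and a two-sided test. The documents give no SD, correlation or expected difference. The change is recommended because it improves precision at almost no cost; the planned comparison is not invalid.

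**What to change.** Rewrite section 2.9 along these lines.

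- The primary analysis is a between-group ANCOVA of eGFR at the named end-of-treatment visit, with baseline eGFR as covariate, reported as an adjusted difference with a 95% confidence interval. Alternatively, use one mixed model over the scheduled visits with baseline, treatment, visit and treatment-by-visit, and the contrast at that visit.
- Skewed variables such as UPCR are analysed by the same model on a log scale fixed in advance, with the log baseline value as covariate, instead of switching to Wilcoxon after seeing the data.
- Within-group changes are reported as means with confidence intervals, without P values, and no claim of efficacy rests on them.

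The cost is one paragraph. Baseline and follow-up renal measurements are already collected, and no extra patients or visits are needed.

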### Data collection and monitoring

2.10

In this 6-month clinical trial, participants will take research medication for at least 8-week and 16-week follow-up. They need to pay regular visit to the research center and fill the evaluation questionnaire. The trial schedule is listed in Figure 2. Researchers are trained to collect trial data carefully according to standard protocol. Molecular biomarkers will be measured triplicated to assure quality. Quality control of data will be achieved throughout the trial process by the clinical center of the First Affiliated Hospital of Soochow University.

### Ethical issues

2.11

This study is approved by the Ethics Committee of the First Affiliated Hospital of Soochow University and the trial protocol is registered at ChiCTR (www.chictr.org, trial identifier ChiCTR1900021622). Written informed consent will be obtained from each participant before enrollment. During the research, participants could withdraw from the trial for any reason at any time. Researchers could remove participants from the trial to ensure their safety or maintain the quality of the trial. Severe adverse event and unexpected adverse event will be reported to the Ethics Committee within 2 days.

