### Study design

2.1

A randomized, parallel, placebo controlled clinical trial will be conducted (Fig. 1). The protocol adheres to the Recommendations for Interventional Trials (SPIRIT) guidelines. This study aims to evaluate the efficacy and safety of Qi Gui Yi Shen decoction in treatment of patients with CKD. The study will follow the guidelines as illustrated in Figure 1. A total of 100 participants recruited form the First Affiliated Hospital of Soochow University in Suzhou are divided into TCM treatment group and placebo group in 1:1 ratio. Both groups are administrated with conventional western medicine treatment while TCM group receive extra Qi Gui Yi Shen decoction and placebo group receive placebo decoction. Patients take medicine 3 times a day for 2 months as 1 cycle. At the same time drug efficacy and safety will be evaluated. The total duration is 6 months in 3 cycles.

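### The open-ended power to remove randomised participants for the sake of trial quality can let outcome-related removals bias the comparison, and should be deleted

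*Protocol article*

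**What the plan says.** Section 2.11 (Ethical issues) first lets participants withdraw at any time for any reason. It then gives the researchers a separate power: "Researchers could remove participants from the trial to ensure their safety or maintain the quality of the trial". It sets no criterion for the quality ground and names no independent or blinded person to make the decision.

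Two sections bear on what the researchers know when they use that power. Section 2.7 (Blind), citing the need for TCM syndrome differentiation during the study, says that "only participants and the laboratory technicians as well as the biostatisticians responsible for the statistical analysis will be blinded". That leaves the clinical researchers out. Section 2.4.3 (Placebo group) says: "Except for the dispensing technician, researchers and patients do not know the content of the drug packages".

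Section 2.8 (Outcome measures) has the primary renal-function measures taken every 2 to 4 weeks and lists TCM symptom change as a secondary outcome. On numbers, section 2.5 (Sample size) says that "the total sample size required is determined to be 98, 49 in each group".

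**The concern.** Randomisation protects the comparison only while the people compared are the people randomised. A ground as broad as trial quality could be applied to a poor adherer, a patient who is worsening, or one enrolled by mistake, and nothing in the article narrows it. Those using it are treating researchers who, on the natural reading of section 2.7, may know the arm.

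Two things are at stake. First, if removals are related to outcome and fall differently on the two arms, the remaining groups are no longer comparable. Second, removal is from the trial, so the visits that would have followed may not take place. A statistical analysis plan can define who is analysed, but it cannot supply measurements that were never made.

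**Working it through.** **Who decides, and what they can see.**
- Under 2.7, researchers are not among the blinded, so removal could depend on arm and on outcome.
- Under 2.4.3, researchers do not know the package content, so deliberate dependence on arm is ruled out. Dependence on outcome is not. The article does not say that renal results or symptom scores are withheld from the researchers.
- On either reading the quality ground allows outcome-related removal. Only 2.7 allows it to follow known arm.

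**Inputs for size.** Section 2.5 gives 49 per group, a t test and α = 0.05. The article does not state sidedness, so two-sided is assumed. It gives no effect size or SD, so the planned total of 98 cannot be re-derived from it. The allowance for loss does fit 39 evaluable per group, since 39 / (1 − 0.20) = 48.75, rounded up to 49. The result below does not depend on that figure. Section 2.1 speaks of 100 participants at 1:1; 50 rather than 49 per arm would change little. The number removed, k, is an assumption.

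**Calculation.** Take a standard normal outcome with no true effect and 49 per arm. Delete the k worst values from one arm and run a two-sided t test. The expected shift in that arm's mean is roughly φ(z_p) / (1 − p) SD, where p = k/49 and z_p is the p-quantile of the standard normal:
- k = 2: p = 0.041, z = −1.74, φ = 0.088, so 0.088 / 0.959 = 0.09 SD.
- k = 5: p = 0.102, z = −1.27, φ = 0.178, so 0.178 / 0.898 = 0.20 SD (0.19 by simulation).

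The standard error of the difference is √(2/49) = 0.20 SD, so these shifts are a little under half to nearly one standard error.

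Simulation of 10,000 to 40,000 null trials per setting:

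| Removed from one arm | Shift (SD) | Two-sided false-positive rate |
|---|---|---|
| none | 0 | 5% |
| 2 worst | 0.09 | 8% |
| 3 worst | 0.12 | 11% |
| 4 worst | 0.16 | 14% |
| 5 worst | 0.19 | 17-18% |

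Most of these false positives favour the trimmed arm: 0.0696 of 0.0807 (86%) at k = 2 and 0.1712 of 0.1738 (99%) at k = 5.

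**Benchmarks.**
- Removing 1 to 10 participants at random from each arm gives no shift and a rate of about 5%.
- A milder selection, taking 4 or 5 at random from the 12 worst in one arm, gives roughly 8-9% and 11%.
- Removing the same number of worst values from both arms gives no shift in the difference under no true effect, by symmetry. The bias therefore needs removal to differ by arm.

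**The case against.** The strongest reply is that the bias is a possibility and not something the plan states. A reader might infer that removed patients are dropped from the analysis and that the comparison is therefore biased. Section 2.11 does not say so, and section 2.9 names no analysis population. That may well be set in a full protocol or analysis plan not shown, so its absence is no finding. With renal function measured every 2 to 4 weeks, a patient removed partway would usually have some post-baseline values that could be kept. All of this stands, and it makes the harm conditional. It does not restore the visits after removal.

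A reader might also infer that the researchers certainly know the arm. The article does not settle that: 2.4.3 says the opposite of 2.7. If 2.4.3 holds, the one-arm mechanism is much weaker, though removal could still follow visible outcomes.

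It is equally tempting to read "considering a drop-out rate of 20" per cent as cover for such removals. Section 2.5 uses that rate for sizing only. Participants' own withdrawal is its obvious source, and nothing links it to removal by researchers.

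Finally, the table is a worst case. A researcher acting mid-trial does not know the final values and could not pick out exactly the lowest. Mistaken enrolment, which need not be related to outcome, is as plausible a use of the quality ground as poor response.

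**Conclusion.** The point holds in a conditional form. The protocol states a rule that lets researchers take randomised participants out of the trial on an unspecified ground, and it contradicts itself on whether those researchers know the treatment. The rule can bias the comparison if removals depend on outcome and differ by arm. It can also lose later data for any participant removed.

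The rise in the two-sided false-positive rate from 5% to about 8-18% is an upper illustration. It assumes 2 to 5 removals, all from one arm of 49, exactly the worst outcomes, a normal outcome, no true effect, and removed participants left out of the analysis. Milder selection gives less, and removal unrelated to outcome leaves about 5%. The documents do not show that biased removal will happen. The case for change is that the ground serves no purpose that recording deviations would not serve, and deleting it is cheap. The safety ground is not in question.

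**What to change.** - In section 2.11, delete the quality ground from the sentence on removal by researchers.
- Add that protocol deviations are recorded and do not lead to removal. Participants who deviate stay on the planned renal-function visits, where they consent, and are analysed in their randomised group.
- Leave the safety ground and its clinical management unchanged. State that data collected up to any safety removal are used in the analysis as randomised.
- Reconcile sections 2.7 and 2.4.3 on whether the researchers are blinded.

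The cost is a few lines of text and some follow-up effort for participants who deviate or are off medication. The visits themselves are already scheduled.
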